#### Proportion of subjects with pain relief at 24 h/7 days/14 days after arterial embolization

To investigate the timing, course, and duration of pain relief in response to arterial embolization, the proportions of subjects with pain relief at 24 h, 7 days, and 14 days are included as other secondary endpoints. The proportion of subjects with pain relief will be assessed based on the Brief-Pain Inventory-Short Form (BPI-SF) questionnaire [15].

The proportion of subjects with pain relief will be calculated using the following equation:3$$proportion of subjects with pain relief = (complete response + partial response)/(FAS - subjects with missing data)$$

where “FAS” stands for “Full Analysis Set,”

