**Fig. 1 Fig1:**
[figure not shown]
Study schema this study consists of two sections, the exploratory and confirmatory phases. Registration will be suspended when 20 subjects are recruited to analyze the data set rather than investigate all the events individually. (Stopping rule) Recruitment of a total of 120 patients is planned

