#### Proportion of subjects with a complete response

To demonstrate that TAE is more effective than placebo, the proportion of complete responders will be assessed.

The proportion of complete responders will be calculated using the following equation:4$$proportion of complete responders = complete response/(FAS - subjects with missing data)$$

The definition of an analysis set is the population of subjects enrolled in the study, excluding those who are doubly or wrongly registered (Table 1).

**Table 1 Tab1:** The definition of each analysis set

Analysis set	Definition
All enrolled subjects	Population of subjects enrolled in the study, excluding those who are doubly or wrongly registered
Full analysis set (FAS)	Population of all enrolled subjects, excluding the following subjects:
	● Subjects who are found ex post facto to be ineligible (fail to meet all of the eligibility criteria or meet any of the exclusion criteria) based on information obtained in accordance with the protocol
	● Subjects who are found to be ineligible based on information obtained after enrollment or unscheduled examination results
	● Subjects who have never received transcatheter arterial embolization (non-implementation)
	● Subjects from whom no data have been collected after enrollment, except information at enrollment into the study
Safety analysis set (SAS)	Population of all enrolled subjects who have been treated with arterial embolization at least once
Per protocol set (PPS)	Population of subjects in the FAS who are in compliance with the protocol

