### Sample size

The clinical hypothesis is that patients with painful bone metastases can be safely treated with arterial embolization for immediate pain relief.

The early response rate after arterial embolization must exceed that after radiotherapy in order for arterial embolization to be established as a new palliative therapy. Since the early response rate was reported to be 26% at 1 week after radiotherapy [16], it is assumed to be lower at 72 h after radiotherapy.

Assuming that the threshold for the proportion of subjects with pain relief at 72 h after arterial embolization, i.e., the primary efficacy endpoint, is 26%, and the expected response rate is 40%, which represents the minimum clinical utility, at least 113 patients are required to provide a power of 90% at a one-sided significance level of 2.5% (normal approximation test).

On the other hand, an adverse event associated with TAE, which is the primary safety endpoint, is defined as any CTCAE Grade 4 adverse event or Grade ≥ 3 CNS necrosis. As described in “Common Adverse Events Associated with Arterial Embolization,” adverse events (including mild events) have been reported in 5% to 7% of patients who undergo arteriography, 10% of patients treated with arterial embolization, and approximately 15% of patients treated with TACE. Considering that patients in poor general condition will be included in this study, the unacceptable threshold incidence for the clinical use of this treatment is set at 15%, equal to that for TACE for hepatocellular carcinoma [17]. Assuming that the incidence will actually be approximately 5% in this study where no anticancer drugs will be used concomitantly; and that bones will be treated, at least 96 patients are required to provide a power of 90% at a one-sided significance level of 2.5% (normal approximation test) (Fig. 1).

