### Statistical methods of analysis

As defined in the Section “Primary Endpoints,” the proportion of subjects with pain relief 72 h after arterial embolization and its two-sided 95% confidence interval (Clopper-Pearson method) will be calculated. It will be determined whether the lower limit of the two-sided 95% confidence interval is > 26%, the threshold response rate established at the time of study design. For reference, the *p*-value will be calculated by a binomial test.

Safety will be evaluated in the Safety Analysis Set (SAS) (Table 2). As defined in “Safety,” the incidence of all CTCAE Grade 4 adverse events and CTCAE Grade ≥ 3 adverse events of CNS necrosis associated with TAE and its two-sided 95% confidence interval (CI) (Clopper-Pearson method) will be calculated. It will be determined whether the upper limit of the two-sided 95% CI is < 15%, the threshold incidence established at the time of study design. For reference, the *p*-value will be calculated by a binomial test.

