### Handling of missing values and outliers

In principle, all analyses will be performed without imputation of missing values or outliers. However, if it is found before data lock that missing values or outliers may significantly affect analysis results, countermeasures will be described in a statistical analysis plan.

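### The only denominator given for pain relief drops subjects with no score, so the 72 h test against 26% is anti-conservative if those subjects respond less often

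*Protocol article*

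**What the plan says.** All places are in the protocol article.

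- **Pain-relief formula.** Equation 3, in the section on pain relief at 24 h, 7 days and 14 days, is "complete response + partial response)/(FAS - subjects with missing data". Equation 4, for complete response, has the same denominator.
- **Primary endpoint.** The Efficacy section names the proportion with pain relief at 72 h and defines a responder as CR or PR. It gives no denominator. Statistical methods of analysis names the safety analysis set for safety but no set for efficacy.
- **Decision rule.** Success depends on "whether the lower limit of the two-sided 95% confidence interval is > 26" (per cent), by the Clopper-Pearson method.
- **Missing data.** In principle, "all analyses will be performed without imputation of missing values or outliers". If missing values are found before data lock to have a possibly significant effect, "countermeasures will be described in a statistical analysis plan".
- **Full analysis set (Table 1).** Among those removed are "Subjects who are found to be ineligible based on information obtained after enrollment or unscheduled examination results", as well as subjects with no data after enrolment. The safety set keeps everyone who was treated.
- **Size.** The threshold for "the primary efficacy endpoint, is 26%, and the expected response rate is 40" (per cent); "at least 113 patients are required to provide a power of 90% at a one-sided significance level of 2.5% (normal approximation test"; and under Fig. 1, "Recruitment of a total of 120 patients is planned". No missing-data rate is stated.

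**The concern.** A treated subject with no 72 h score leaves both numerator and denominator. Eligible patients use opioids, have a pain score of at least 5 and need only a life expectancy above 1 month. Some may give no score because they died, were sedated or deteriorated, and such subjects have not obtained the benefit that the trial is meant to show. Removing them raises the observed response rate. In a randomised trial a similar loss might occur in both arms. Here the comparison is with a fixed 26%, so nothing offsets it.

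Two further features add to this. The full analysis set allows a treated subject to be removed on information that arrives after enrolment, in a trial where outcomes are open. The missing-data section also lets the handling change once missing values are seen to matter, and nobody making that decision is blind to outcome. At stake is the error rate of the primary decision.

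**Working it through.** **Inputs.** p0 = 26%, p1 = 40%, one-sided 2.5%, power 90%, n = 113 (Sample size); 120 planned (Fig. 1); success if the Clopper-Pearson lower limit exceeds 26% (Statistical methods of analysis). The numbers missing, m, and the response rate of missing subjects, p_m, are assumptions.

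**1. The plan's own figure.** n = [(1.960·√(0.26·0.74) + 1.282·√(0.40·0.60)) / 0.14]² = 112.9, so 113. The stated figure reproduces. The sample size formula is not at fault.

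**2. Rule with nothing missing.** With n = 120, success needs 42 responders (35.0%, lower limit 26.5%). The exact false-success probability at 26% is 1.8%, and power at 40% is 88.8%.

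**3. Complete-case rule with m missing.** Let the rate among all 120 treated be 26%. The rate among those observed is then

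p_obs = (0.26·120 − m·p_m) / (120 − m).

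False success is P(X ≥ r), with X binomial(120 − m, p_obs) and r the smallest success count at n = 120 − m. With p_m = 0:

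| m | observed n | r | p_obs | false success |
|---|---|---|---|---|
| 0 | 120 | 42 | 26.0% | 1.8% |
| 3 | 117 | 41 | 26.7% | 2.8% |
| 6 | 114 | 40 | 27.4% | 4.3% |
| 12 | 108 | 38 | 28.9% | 9.2% |
| 18 | 102 | 36 | 30.6% | 17.7% |

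The benchmark is the nominal 2.5%, of which 1.8% is attained with none missing.

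**4. Dependence on p_m, with m = 12 (n = 108, r = 38).**

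| p_m | p_obs | false success |
|---|---|---|
| 0% | 28.9% | 9.2% |
| 13% | 27.4% | 4.8% |
| 26% | 26.0% | 2.2% |
| 40% | 24.4% | 0.8% |

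**5. Results that change the conclusion.** 38/108 = 35.2%, lower limit 26.2%, success; 38/120 = 31.7%, lower limit 23.5%, failure. Likewise 40/114 has lower limit 26.4%, success; 40/120 has 25.0%, failure.

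**6. Missing counted as non-response.** Success needs 42 of 120 whatever m is. Under the assumptions of step 3, false success stays at or below 1.8%. The price appears if scores are missing purely at random and the true response is 40%. Power is then P(X ≥ 42) with X binomial(120 − m, 0.40):

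| m | power, missing = non-response | power, complete-case |
|---|---|---|
| 0 | 88.8% | 88.8% |
| 3 | 84.1% | 88.3% |
| 6 | 78.3% | 87.9% |
| 12 | 62.8% | 86.9% |

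**The case against.** **Equation 3 belongs to the secondary time points.** This is true of its placing, so its use at 72 h is an inference. The inference is well supported: the quantity has the same name, no other denominator is offered, and the no-imputation default covers all analyses. Nowhere is a subject without a score counted as a non-responder.

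**Missing scores may be few and uninformative.** Patients are inpatients, must be able to rate pain, and report electronically within a window of ± 3 h. A missed window or a device fault is as plausible a cause as deterioration. This stands. A reader might infer that the primary test is biased towards success as a matter of fact. The documents do not support that: they give neither a missing rate nor the reasons for missing scores, and step 4 shows no inflation when missing subjects respond at the common rate.

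**Removing ineligible subjects is not shown to favour TAE.** This also stands. Pain response is not an eligibility criterion, and the documents show no direction of effect. What remains is that treated subjects can be removed on later information in an open trial.

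**The analysis plan may deal with it.** The no-imputation rule is qualified as a principle, and any countermeasure must be identified before data lock. But the article does not merely leave the matter open. It prints a complete-case denominator and makes departure from it depend on what the accumating data show.

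**Conclusion.** The point holds in conditional form. The protocol prints a complete-case denominator for pain relief and gives the 72 h primary endpoint no other. If subjects without a 72 h score respond less often than those with one, the test against 26% is anti-conservative. With 120 treated and every missing subject a non-responder, false success already exceeds the nominal 2.5% slightly at 3 missing (2.8%) and reaches 9.2% at 12. With 12 missing it is 4.8% if 13% of them respond and 2.2% if 26% do. All missing counts and response rates among the missing are assumptions, so the actual size is unknown.

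The exclusion of treated subjects on later information is a weakness of unknown direction and adds nothing to these figures. This should be fixed; confidence is moderate, because the link to the 72 h endpoint is inferred and the extent of missing data is not known.

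**What to change.** - State that the primary 72 h analysis includes all subjects who received TAE, with a missing 72 h assessment counted as non-response.
- Use the same denominator and rule in equations 3 and 4.
- Keep the complete-case and eligible-only analyses as sensitivity analyses.
- Limit the clause on later countermeasures to additional sensitivity analyses, so that the primary handling is fixed before outcomes are reviewed.

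**Cost.** The change of wording is small, but the change is not free. The observed rate will be somewhat lower, and power falls as in step 6 if scores are missing purely at random. The planned 120 exceeds 113 by only 7, and the article reports enrolment under way. The stated 90% power should therefore be restated for the expected missing rate, and missing 72 h scores should be kept few.

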#### Proportion of subjects with an improvement in Karnofsky Performance Score (KPS)

An improvement in KPS would provide an additional reason to use TAE instead of other methods. The proportion of subjects with an improvement in KPS is included as another secondary endpoint. An increase or decrease of ≥ 1 level will be counted as a significant change.

#### Proportion of subjects with a complete response

To demonstrate that TAE is more effective than placebo, the proportion of complete responders will be assessed.

The proportion of complete responders will be calculated using the following equation:4$$proportion of complete responders = complete response/(FAS - subjects with missing data)$$

The definition of an analysis set is the population of subjects enrolled in the study, excluding those who are doubly or wrongly registered (Table 1).

**Table 1 Tab1:** The definition of each analysis set

Analysis set	Definition
All enrolled subjects	Population of subjects enrolled in the study, excluding those who are doubly or wrongly registered
Full analysis set (FAS)	Population of all enrolled subjects, excluding the following subjects:
	● Subjects who are found ex post facto to be ineligible (fail to meet all of the eligibility criteria or meet any of the exclusion criteria) based on information obtained in accordance with the protocol
	● Subjects who are found to be ineligible based on information obtained after enrollment or unscheduled examination results
	● Subjects who have never received transcatheter arterial embolization (non-implementation)
	● Subjects from whom no data have been collected after enrollment, except information at enrollment into the study
Safety analysis set (SAS)	Population of all enrolled subjects who have been treated with arterial embolization at least once
Per protocol set (PPS)	Population of subjects in the FAS who are in compliance with the protocol

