### Study setting

This study is a multicenter, single-arm confirmatory study to clarify the efficacy and safety profile of TAE for painful bone metastases (phase 2–3 design).

All participants will be recruited from 24 hospitals: Aichi Medical College, Aichi Cancer Center, Iwate Medical College, Cancer Institute Hospital of JFCR, Tonan Hospital, National Cancer Center Hospital, National Cancer Center Hospital East, Shizuoka Cancer Center, Juntendo Hospital, Teina Keijinkai Hospital, Hokkaido University Hospital, Ryukyu University Hospital, Osaka University, Kobe University, Keio University, Saiseikai Fukuoka Sogo Hospital, Nara City Hospital, Hakodate Goryokaku Hospital, Hyogo Cancer Center, Hyogo Medical University, Fukuchiyama City Hospital, Nara Medical Hospital, St. Marianna University Hospital, and Hokkaido Cancer Center.

The protocol treatment will be performed on inpatients.

To ensure the safety of subjects, registration will be suspended to evaluate safety once 20 subjects are recruited. In the exploratory phase, if any CTCAE Grade 4 adverse event or a Grade 3 or higher adverse event of central nervous system (CNS) necrosis occurs in at least 4 of the 20 subjects, the study will be discontinued (stopping rule) (Fig. 1).

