### Masking

This is not a blinded study for either clinicians or patients.

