## Discussion

In this study, we will examine the effect of TAE in providing immediate pain relief (within 3 days) for painful bone metastases. Palliative radiotherapy is one of the most commonly used modalities for painful bone metastases; however, its median time to pain relief is 4–8 weeks. Painkillers, including opioid analgesics, temporarily relieve pain but do not remove its cause. Therefore, a modality which can achieve immediate pain relief and remove its cause is necessary in this field. TAE may have the potential to achieve these goals.

Since there is no standard treatment to compare with TAE for relieving bone metastatic pain in as short as a few days, this study will be conducted with a single arm. Because no quickly effective standard treatment is available, TAE, if shown to be quickly effective, will serve as a useful treatment option in clinical practice. In that case, TAE will be practically handled as one of several standard approaches; therefore, this study will be conducted as a confirmatory study. The study will also be conducted as a single-arm confirmatory study without controls in accordance with the Research Policy of Supportive and Palliative Care in Japan [18].

Because TAE’s safety and efficacy have not been confirmed in a palliative setting, a prospective confirmatory trial is needed. Considering that palliative radiotherapy, pain killers, and TAE can be combined, we feel a randomized control study design comparing TAE with these other modalities is not necessary. In order to preserve the reliability of the results, we will evaluate efficacy and safety by maintaining strict thresholding and stopping rules.

TAE is not a major tool in this field at present. If the primary and co-primary endpoints are met, TAE can be a treatment choice for painful bone metastases, and these results will potentially provide many benefits for all eligible patients with painful bone metastases.

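### The complete-response endpoint is given the purpose of showing superiority to placebo, which a single-arm, uncontrolled, open-label trial with no placebo rate cannot show

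*Protocol article*

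**What the plan says.** In the protocol article, the section on the proportion of subjects with a complete response opens with the purpose of the endpoint: "To demonstrate that TAE is more effective than placebo, the proportion of complete responders will be assessed". The estimator (equation 4) is "proportion of complete responders = complete response/(FAS - subjects with missing data", with the bracket closed after it. It has no comparator term and no reference value.

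The design is fixed elsewhere in the same article:

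- Study setting: "This study is a multicenter, single-arm confirmatory study".
- Discussion: "The study will also be conducted as a single-arm confirmatory study without controls". The reason given is "Since there is no standard treatment to compare with TAE for relieving bone metastatic pain in as short as a few days". That reason concerns an active standard treatment; placebo or sham is not discussed.
- Masking: "This is not a blinded study for either clinicians or patients".
- Allocation: stated not to apply.

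The one efficacy benchmark is in the Sample size section, where the threshold for pain relief at 72 h "is 26%, and the expected response rate is 40%, which represents the minimum clinical utility". The article takes the 26% from a report of response 1 week after radiotherapy. Under Efficacy, a responder to the primary endpoint is a subject with either complete or partial response.

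**The concern.** To say that a treatment beats placebo is to make a comparative claim. It needs either patients who received placebo or, much more weakly, a credible external placebo rate for the same outcome. The article provides neither, yet it states the comparison as the purpose of the endpoint.

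Pain is rated by patients who know they have been treated, and entry requires a pain score of at least 5 out of 10. Expectation and regression to the mean are what a placebo comparison is meant to separate from the treatment effect, and one proportion in treated patients cannot separate them.

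What is at stake is the wording of the eventual report. The trial calls itself confirmatory, and the Discussion foresees TAE being handled as one of several standard approaches if it proves quickly effective. A prespecified purpose of superiority to placebo would give a results paper apparent cover for a claim that the data cannot carry.

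**Working it through.** **1. Does any stated figure relate to placebo or to complete response?**

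The article's two sample sizes were reproduced with the one-sample normal approximation, n = [z(0.975)·√(p0(1−p0)) + z(0.90)·√(p1(1−p1))]² / (p1−p0)². All inputs come from the Sample size section.

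- Efficacy, p0 = 0.26 and p1 = 0.40: [1.960 × √0.1924 + 1.2816 × √0.24]² / 0.14² = 112.90, so 113. This matches the stated 113.
- Safety, p0 = 0.15 and p1 = 0.05: [1.960 × √0.1275 + 1.2816 × √0.0475]² / 0.10² = 95.87, so 96. This matches the stated 96.

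Both figures are therefore fully explained by the 72 h response threshold and the safety threshold. Neither contains a placebo rate or a complete-response rate.

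**2. What each part of the claim would need, and what the article supplies**

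| Needed for superiority to placebo | Supplied in the protocol article |
|---|---|
| Concurrent placebo or sham group | None: single arm, no controls, no allocation |
| Blinding of the patient-reported outcome | None: open to clinicians and patients |
| External placebo rate | None: the word placebo occurs only in the purpose sentence |
| Reference value for complete response | None: 26% is a radiotherapy rate at 1 week, used for complete plus partial response |
| Test or decision rule for complete response | None: Statistical methods gives rules only for 72 h pain relief (lower limit above 26%) and safety (upper limit below 15%) |

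**3. Does the trial's conclusion depend on this endpoint?**

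No. The Abstract rests the conclusion on the primary and secondary endpoints, and it names the safety endpoint as the secondary one. The Discussion speaks of primary and co-primary endpoints. Complete response is outside both statements.

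**4. Illustration only: what an external rate would have to settle**

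The placebo complete-response rates below are assumptions, since the article gives none. The rule, that the lower 95% Clopper-Pearson limit exceeds the assumed rate, is borrowed from the primary endpoint and is not planned for this one. With n = 120, the planned recruitment, the smallest qualifying number of complete responders is:

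| Assumed placebo rate | Smallest count of 120 | Observed proportion |
|---|---|---|
| 1% | 5 | 4.2% |
| 2% | 7 | 5.8% |
| 5% | 12 | 10.0% |
| 10% | 20 | 16.7% |
| 20% | 34 | 28.3% |

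Twelve complete responders of 120 (95% interval 5.3% to 16.8%) would lie above an assumed 5% but not above an assumed 10%. The answer turns on a number that the article does not fix. Even with that number fixed, the result would be a comparison with a historical threshold and would not demonstrate an effect against placebo.

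**The case against.** The best defence is that the sentence is only a rationale. Neighbouring secondary endpoints open in the same manner: improvement in KPS is offered as an added reason to use TAE, and relief of motion pain as clinically significant. Complete response may have been chosen because complete disappearance of pain is hard to attribute to placebo. The only operative instruction is to calculate an ordinary proportion. A benchmark for it might also sit in the full protocol or the SAP, neither of which is shown.

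Much of this stands, and it limits the weight of the point. It does not rescue the stated purpose. The article does not say that complete response is rare under placebo and gives no rate to support that. Such an argument would justify choosing the endpoint but not claiming a demonstration from it. A fuller document could add a threshold, but an SAP could not add a placebo arm or blinding.

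A reader might also infer several stronger points, which the article does not support:

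- *Any complete-response rate will be declared proof against placebo, with an uncontrolled error rate.* No placebo test is planned, so there is no error rate to speak of.
- *The complete-response rate is a 72 h figure.* The section gives no assessment time for it.
- *Permitted analgesics inflate the rate.* Response follows a cited consensus whose definition of complete response is not reproduced, and Table 2 records daily morphine quantity at every assessment. Whether greater analgesic use could coexist with a complete response cannot be judged here.
- *The exclusion of missing data is part of this fault.* Equation 3 uses the same denominator, and it has no bearing on the placebo claim.

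**Conclusion.** The point holds as a mismatch between stated purpose and design. With one arm, no controls, no blinding and no placebo rate, the complete-response proportion can describe how deep the response is among treated patients. It cannot demonstrate that TAE is more effective than placebo.

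No numerical size can be attached, and no figure in the article needs correcting; the stated 113 and 96 both reproduce. The consequence is confined to what the report may claim from one secondary endpoint. The primary analysis, the safety analysis and the criteria for success are unaffected. The conclusion rests on the text of the article alone and on no assumed rate.

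**What to change.** In the section on complete response, replace the purpose with wording such as *to describe the depth of response*. Report the proportion with its two-sided 95% Clopper-Pearson interval, the method that Statistical methods already specifies for the primary and safety endpoints. Add that no conclusion about placebo will be drawn from it.

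The cost is one reworded sentence, one added sentence and one interval. No data, patients or sample-size change are needed, and the only loss is a claim that the trial could not support.

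Leave the denominator of equation 4 as it is for this purpose. Any change to how missing data are counted is a separate decision and should be made for equations 3 and 4 together.
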